## Abstract

**Background:**

Pelvic inflammatory disease (PID) is common and can lead to tubal factor infertility, ectopic pregnancy or chronic pelvic pain. Despite major UK government investment in the National Chlamydia Screening Programme, evidence of benefit remains controversial. The main aim of this trial was to investigate whether screening and treatment of chlamydial infection reduced the incidence of PID over 12 months. Secondary aims were to conduct exploratory studies of the role of bacterial vaginosis (BV) in the development of PID and of the natural history of chlamydial infection.

**Design:**

Randomised controlled trial with follow up after 12 months.

**Setting non-healthcare:**

Common rooms and lecture theatres at 20 universities and further education colleges in Greater London.

**Participants:**

2500 sexually active female students were asked to complete a questionnaire on sexual health and provide self-administered vaginal swabs and smears.

**Intervention:**

Vaginal swabs from intervention women were tested for chlamydia by polymerase chain reaction (PCR) and those infected referred for treatment. Vaginal swabs from control women were stored and analysed after a year. Vaginal smears were Gram stained and analysed for BV.

**Main outcome measure:**

Incidence of clinical PID over 12 months in intervention and control groups. Possible cases of PID will be identified from questionnaires and record searches. Confirmation of the diagnosis will be done by detailed review of medical records by three independent researchers blind to whether the woman is in intervention or control group.

**Trial registration:**

Clinical Trials NCT 00115388

## Background

Pelvic inflammatory disease (PID) is the most important preventable bacterial sexually transmitted infection in industrialised countries[1]. Studies in clinical settings suggest 15–50% of cases are caused by *Chlamydia trachomatis *infection[1]. After one episode of PID around 15% of women may become infertile, 10% suffer chronic pelvic pain and 10% of subsequent pregnancies may be ectopic which can be life threatening. The financial cost of treating PID and its sequelae, particularly tubal factor infertility, is considerable, quite apart from the emotional and physical costs to the woman.

There has been only one major trial in non-pregnant women of chlamydia screening to prevent PID[2]. This was conducted over 15 years ago in an American population using tests which have been superseded [2-4]. Before chlamydial screening became widespread in the UK, around 2006–2008, there was a window of opportunity to conduct a trial of community based screening using new nucleic acid amplification tests and non-invasive screening in a young, multiethnic, female student population[3].

In order to prevent chlamydia associated PID we also need to understand more about the natural history of chlamydial infection in women, and about the role of possible co-factors such as bacterial vaginosis (BV). Studies to date have been small[5] or cross-sectional[6], and a larger prospective study is needed[3]. We developed a special screening pack to test for chlamydia and BV using self-administered vaginal swabs[7]. The method was acceptable even during pregnancy and was used in our feasibility study in a student bar recruiting women to a trial of chlamydia screening[8]. The POPI (Prevention of Pelvic Infection) trial should provide new information on the effectiveness of screening for chlamydia, the possible role of bacterial vaginosis, and the natural history of chlamydial infection in the community.

## Methods/Design

### Primary aim

To investigate if screening young female students for chlamydial infection and treating those found to be infected reduces the incidence of PID in the subsequent 12 months.

### Secondary aims

We will conduct exploratory studies to investigate:

1. The role of BV at baseline on the development of PID over 12 months.

2. In women with untreated chlamydial infection, the proportion who have persistent infection or develop PID within 12 months.

3. The annual incidence of chlamydia infection in women without chlamydia at baseline who return follow up postal samples.

### Design

Randomised controlled trial over one year

The flow of participants through the trial is shown in figure 1.

**Figure 1 F1:**
[figure not shown]
Design and timetable of trial of screening for chlamydia to prevent pelvic inflammatory disease (PID).

### Setting

Common rooms, bars and lecture theatres at 20 universities and further education colleges in Greater London.

Following agreement from the Students' Union Presidents, College Principals and welfare officers, posters about the study were displayed on the Students' Union website and notice boards. Recruitment was done by the research general practitioner (GP) and female research assistants assisted by trained peer recruiters as necessary.

### Participants

Sexually experienced female students aged ≤ 27 years were eligible for the study. Pregnant women, those who had never been sexually active, women aged >27, and women who had been tested for chlamydia in the past 3 months were excluded.

### Recruitment

Women considering taking part were given an information leaflet and invited to discuss the study with the research assistants or GP. Those who decided to participate were asked to sign a consent form, to complete a brief confidential questionnaire on sexual health and behaviour, to provide self-administered vaginal swabs in the nearest lavatory, and to consent to access to their medical records for the purposes of this study.

The baseline questionnaire asked about risk factors for chlamydial infection[9]: age, ethnicity, age at first sexual intercourse, number of sexual partners in the past year, contraceptive use; possible symptoms of infection: abnormal vaginal discharge, pelvic pain, dyspareunia, intermenstrual or post-coital bleeding; recent antibiotic treatment; history of sexually transmitted infection (STI); vaginal douching, smoking and quality of life (EQ-5D). To simplify recruitment, illustrated instructions on how to provide a self-administered vaginal swab were printed on specimen packs and displayed in the nearest lavatory, and specimen containers were prelabelled[7].

### Intervention

Within two weeks of recruitment participants were randomly allocated into two groups by researchers at St George's, University of London using random number tables starting with a number at any position and going consistently in any direction. Consecutive sealed specimen packs identified only by an ID number were taken out of the large carrier bag into which they had been put during recruitment sessions. If the random number ended in 0–4 the pack was put into the intervention pile; if it ended in 5–9 the pack was put into the control pile. Vaginal swabs were taken out of the specimen packs in the intervention pile and sent to the laboratory to be tested for chlamydial infection by transcription mediated amplification (TMA, Gen-Probe Incorporated San Diego, CA). Vaginal swabs from control women were stored at -80°C and analysed one year later. Infected women were contacted as soon as possible by the research GP and asked to attend their local Genitourinary Medicine (GUM) Clinic or GP for treatment and partner notification. One month later, the research GP telephoned the women again to answer any questions and to ensure that both they and their partner(s) had completed a course of treatment.

### Follow up after one year

A year after recruitment, participants were asked to complete a secure online questionnaire about PID symptoms during the previous 12 months. Those not responding or not providing an email address were sent the questionnaire by post backed up by telephone reminders. In order to maximise follow up, consent forms requested details of home and term time addresses and telephone numbers, email, mobile phone number, college course and GP address. The questionnaire asked about possible symptoms of, or treatment for, PID or other STI, any additional STI testing, and hospital and GP attendances in the past year. Women who reported no symptoms of possible PID on their questionnaire had no further follow up. For women who did not return a questionnaire and those who reported consulting a health professional for possible symptoms of PID we sent a questionnaire to their GPs. This asked GPs to search both their records and any hospital letters during the 12 month period after recruitment for possible symptoms of PID. In addition, all women who agreed on their follow up questionnaire to return a further swab were sent one in the post. These postal samples were analysed immediately and infected women referred for treatment.

### Further analysis of vaginal samples

A year after recruitment we analysed stored baseline vaginal swabs from women in the control group. Women whose swabs were positive for chlamydia were referred to GUM for retesting and treatment. Vaginal smears taken at baseline were Gram stained and examined for BV using Nugent's criteria[7]. Slides were read by two observers who were blinded to each other's results, to characteristics of participants and to outcome in terms of PID. Slides were categorised as positive (Nugent score 7–10), intermediate (4–6) or negative (0–3). Where the observers disagreed, the slide was reviewed until consensus was reached. There is little evidence that asymptomatic BV is harmful in non-pregnant women and no treatment was given. Participants worried about infection were advised to have a check up.

### Outcome measures

#### Primary outcome measure in the complete cohort

Incidence of clinical PID over 12 months in intervention and control groups.

Possible cases of PID will be identified from patient and GP 12 months questionnaires reporting pelvic infection, abdominal or pelvic pain or dyspareunia. For women who consulted a healthcare professional for these symptoms we will try to obtain clinical records including information on symptoms, findings on examination and laboratory results, excluding chlamydia results from trial samples. We will also try to obtain details on any woman reporting she had a laparoscopy in the follow up period. Since it would be unethical to demand a laparoscopic diagnosis of PID, as in the Scholes et al trial[2] we will use a modified version of Hager's clinical criteria[10] where details are provided in the medical records: lower abdominal pain, adnexal tenderness and tenderness on cervical motion. If available we will also include the results of concurrent microbiological tests and clinical data on fever >38°, leucocytosis >10,000, purulent material or pelvic abscess. To reduce bias, confirmation of the diagnosis will be done by review of all data (anonymised questionnaires and clinical records) by two independent GUM physicians (with review by a third where they disagree) who will be blind as to whether the patient is in intervention or control group.

#### Secondary outcome measures

We will conduct exploratory studies to investigate:

1. The role of BV at baseline on the development of PID over 12 months.

2. In women with untreated chlamydial infection, the proportion who have persistent infection or develop PID within 12 months.

3. The annual incidence of chlamydia infection in women without chlamydia at baseline who return follow up postal samples,

#### Blinding

The GU physicians will be blind to group assignment. They will categorise cases of PID as probable, possible or not PID, for example if subsequent laparoscopy suggests the pain is due to endometriosis. The research assistant who selected the questionnaires and anonymised the medical records for assessment for possible PID was also blind to study group assignment.

All participants were blind except those in the intervention group whose baseline samples were positive for chlamydia and who were referred for treatment. It is possible that the principle investigator who contacted women to tell them they were chlamydia positive might remember some names when assisting with obtaining medical records for follow up 1–2 years later. There was a change of research assistant between recruitment and final follow up. The research assistant doing the final follow up for PID diagnosis was not involved in randomization or testing and treatment of chlamydia positives. Both she and the PI had access to group allocation but avoided looking at this during follow up.

### Sample size calculations

Assuming a 2% incidence of PID, a sample size of 4122 women would allow a relative risk (RR) of 0.48 to be detected with 80% power using a 5% significance level. This was based on data from the Scholes et al trial[2] where the rate of chlamydia was 7%. Assuming 20% of women were lost to follow up, we would have needed to recruit 5000 women.

However we had great difficulties with recruitment, and a publication in 2004 suggested a higher rate of PID[11] enabling us to revise down our sample size calculations. If we assume a 3% incidence of PID in the control group[11,12], we would need a sample of 2274 women to detect a RR of 0.44% with 80% power and 5% significance. Details on the consent form provided up to 7 potential contact methods for follow up, and we achieved 92% follow up after 8 months in the feasibility study[8]. To reduce bias we aimed to keep loss to follow up at 12 months below 10%. Assuming 10% loss to follow up we needed to recruit 2501 women.

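### The recruitment target of 2501 adds 10% to 2274 instead of dividing by 0.90, so at the stated 10% loss it falls 23 evaluable women short; the effect on power is small

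*Protocol article*

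**What the plan says.** All the figures are in the protocol article, under Sample size calculations.

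- **Operative (revised) calculation.** The premise is "If we assume a 3% incidence of PID in the control group". From it the article concludes "we would need a sample of 2274 women to detect a RR of 0.44% with 80% power and 5% significance". (The printed percent sign after 0.44 is read here as a slip; the value works as a relative risk of 0.44.) The allowance for loss follows: "Assuming 10% loss to follow up we needed to recruit 2501 women".
- **Aim for follow-up.** "To reduce bias we aimed to keep loss to follow up at 12 months below 10" per cent. As support, the article reports that "we achieved 92% follow up after 8 months in the feasibility study".
- **Superseded (original) calculation.** The starting point is "Assuming a 2% incidence of PID, a sample size of 4122 women". The target effect was an RR of 0.48, at the same power and significance level as in the revised design. The allowance for loss is: "Assuming 20% of women were lost to follow up, we would have needed to recruit 5000 women".

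No inflation formula is given for either target.

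**The concern.** For each design the article gives three linked figures: the number needed for 80% power, the assumed loss, and the number to recruit. The third should follow from the first two, because recruits × (1 − loss) should return the number needed. In neither case does it.

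For the operative target the reason is visible. The stated 2501 is the required number plus 10% of itself, whereas the loss is taken from the larger number recruited. The recruitment target is a headline design figure, and a reader who checks it finds that it misses the required sample under the plan's own assumption. What is at stake is the internal consistency of the sample-size statement and, to a small extent, the power.

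**Working it through.** **Inputs, all from Sample size calculations unless noted**

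- Revised: control incidence 3%, relative risk 0.44, 2274 women needed, 10% loss, target 2501.
- Original: incidence 2% (taken as the control-group rate), relative risk 0.48, 4122 women needed, 20% loss, target 5000.
- Both: 80% power, 5% significance. Sidedness is not stated. Two-sided is assumed, because one-sided totals would be 1850 and 3332, far from the stated numbers.
- Allocation 1:1, from the Intervention section (last digit 0–4 against 5–9).

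**Step 1. Can the stated evaluable numbers be reproduced?**

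Pooled-variance formula, with n per arm, p1 the control risk, p2 = RR × p1, and p̄ their mean:

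power = Φ{ [√n (p1 − p2) − 1.96 √(2p̄(1 − p̄))] / √(p1(1 − p1) + p2(1 − p2)) }

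- Revised: p1 = 0.03, p2 = 0.0132, p̄ = 0.0216. The total for 80% power is 2350, against 2274 stated (3.3% off). With a relative risk of 0.435, which rounds to 0.44, it is 2300 (1.1% off).
- Original: p1 = 0.02, p2 = 0.0096, p̄ = 0.0148. The total is 4232, against 4122 stated (2.7% off).
- Continuity-corrected totals (2582 and 4608) do not fit.

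The stated 2274 and 4122 are therefore accepted, allowing for rounding of the relative risk and the choice of formula.

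**Step 2. How was the target obtained?**

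| | Needed | Loss | Needed × (1 + loss) | Needed / (1 − loss) | Stated target |
|---|---|---|---|---|---|
| Revised | 2274 | 10% | 2501.4 | 2526.7, so 2527 | 2501 |
| Original | 4122 | 20% | 4946.4 | 5152.5, so 5153 | 5000 |

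The stated 2501 is the multiplied figure with the fraction dropped. The stated 5000 matches neither column. It could be 4946 rounded up, but the article does not say so.

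**Step 3. What does each target deliver at the stated loss?**

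- Revised: 2501 × 0.90 = 2250.9, about 2251. Shortfall 2274 − 2251 = 23 evaluable women (1.0%); 2527 − 2501 = 26 more to recruit.
- Original: 5000 × 0.80 = 4000. Shortfall 4122 − 4000 = 122 evaluable women (3.0%); 5153 − 5000 = 153 more to recruit.
- Break-even loss for the revised target: 1 − 2274/2501 = 9.1%.

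**Step 4. Cost in power, same formula on both sides**

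- Revised, at 2274 (n = 1137): numerator 33.719 × 0.0168 − 0.4029 = 0.1635; divided by 0.2052 this is 0.797, so power is 78.7%.
- Revised, at 2251 (n = 1125.5): numerator 33.548 × 0.0168 − 0.4029 = 0.1607; divided by 0.2052 this is 0.783, so power is 78.3%. Difference 0.4 points.
- Original: 79.0% at 4122 and 77.8% at 4000. Difference 1.2 points.
- With a relative risk of 0.435 in the revised design: 79.6% at 2274 and 79.2% at 2251. The difference is again 0.4 points.

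**The case against.** The strongest reply is that the slip has almost no consequence. The operative gap is 1.0% of the target and 0.4 power points, small beside the uncertainty in the assumed 3% incidence. The article aimed for loss below 10%, not for 10% exactly. If loss is at most 9.1% the target is enough, and at the feasibility study's 92% follow-up it gives 2501 × 0.92 = 2301 women, above 2274. Recruitment is reported as finished in October 2006, so nothing in conduct can change. The 5000 target was replaced and no current figure depends on it.

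All of this stands as a limit on the size of the point. It does not remove the error. The target is introduced with an assumption of 10% loss, and under that assumption it does not return 2274. Loss between 9.1% and 10% would meet the article's aim and still miss its required sample.

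Three stronger readings are tempting, and the document supports none of them.

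- *The slip takes power from 80% to about 78%.* By the same formula power is already 78.7% at 2274. Most of the gap to 80% reflects the choice of formula and the rounding of the relative risk, not the allowance for loss.
- *Both targets come from the same wrong operation.* That is shown for 2501 only. For 5000 the shortfall is certain but the operation is not.
- *The 92% follow-up at 8 months implies about 88% at 12 months, so the 10% allowance is too small.* This needs a constant rate of loss over time, which the article does not assume. The article also describes up to seven contact methods, and a questionnaire to the GPs of women who do not reply, which may limit loss for the primary outcome.

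**Conclusion.** The point holds as a minor arithmetic error. The operative target should be 2527, not 2501, if 2274 evaluable women are to remain after 10% loss; as printed it leaves about 2251. The superseded target is inconsistent too: 4000 remain against 4122, and 5153 would have been needed.

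The shortfalls rest only on the article's own numbers and on reading loss as a share of the women recruited. The power differences also rest on a two-sided pooled test with 1:1 allocation. The document does not support a claim that this slip leaves the trial materially underpowered.

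**What to change.** Either correct the two recruitment figures to 2274/0.90 = 2527 and 4122/0.80 = 5153, or keep a target of about 2500 and add that 10% loss leaves about 2250 evaluable women, with power about 0.4 points below that at 2274. If a power figure is printed, give the value at 2274 by the same formula beside it, so that the difference is not mistaken for the whole gap to 80%.

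The cost is a change of wording. Recruitment, follow-up and analysis are unaffected.

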### Analysis Plan

For the primary analysis, we will estimate the relative risk of developing PID in the 12 months after recruitment in the intervention group compared with the control.

In secondary analyses, we will conduct an exploratory logistic regression to adjust the RR of development of PID for the presence of baseline BV.

We will conduct further exploratory analyses to assess:

In women with untreated chlamydial infection, the proportion (95%CI) who have persistent infection or develop PID within 12 months.

The annual incidence (95%CI) of chlamydia infection in women without chlamydia at baseline who return follow up postal samples.

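### The primary RR is valid as stated but leaves baseline risk items unused; a pre-specified adjusted RR would be a small gain, and the BV logistic model gives an odds ratio, not the RR it names

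*Protocol article*

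**What the plan says.** The Protocol article, under the heading Analysis Plan, sets the main analysis in one sentence: "For the primary analysis, we will estimate the relative risk of developing PID in the 12 months after recruitment". The contrast is intervention against control. No covariate is named, and the word unadjusted is not used. Adjustment appears once, as a secondary analysis: "we will conduct an exploratory logistic regression to adjust the RR of development of PID for the presence of baseline BV".

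Recruitment section: "The baseline questionnaire asked about risk factors for chlamydial infection". The items include age, "number of sexual partners in the past year, contraceptive use; possible symptoms of infection: abnormal vaginal discharge, pelvic pain, dyspareunia", and also history of sexually transmitted infection.

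Intervention section: allocation follows collection of these data ("Within two weeks of recruitment participants were randomly allocated into two groups") and is made by random digits: "If the random number ended in 0–4 the pack was put into the intervention pile", and otherwise into the control pile. No blocking or stratification is described.

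Sample size calculations: 3% control incidence, RR 0.44 (printed with a stray percent sign), 2274 women, 80% power, 5% significance; 2501 to be recruited, allowing for 10% loss.

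**The concern.** Simple randomisation over 20 institutions balances baseline risk only on average. Several recorded items could plausibly relate to PID. The Background attributes 15–50% of clinical PID cases to chlamydia, and the Recruitment section lists risk factors for chlamydia. Pelvic pain and dyspareunia at baseline are also among the reports that flag a possible case at 12 months, and the eligibility criteria do not exclude women who already have them.

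The one covariate chosen for adjustment, BV, is there because it is a secondary research question. The article does not argue that it is the best prognostic variable.

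At stake are a little precision and protection against later argument. If a reader asks for an adjusted result once the outcome is known, a covariate list chosen at that stage is open to question. The Blinding section says the principal investigator and the follow-up research assistant had access to allocation, although they avoided looking at it.

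A second, smaller matter is that the model named for the BV analysis does not directly yield the effect measure named for it.

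**Working it through.** **Inputs from the Protocol article.** Control risk 0.03; RR 0.44, so intervention risk 0.03 × 0.44 = 0.0132; 2274 evaluable women; 2501 recruited, of whom 2501 × 0.90 = 2251 are followed; expected allocation 1:1.

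**Inputs assumed.** The article gives neither the prevalence of the baseline items nor their association with PID. Four binary covariates were assumed, with prevalences 15%, 35%, 30% and 10% and PID risk ratios of either 3, 2, 1.5, 2 or 4, 3, 1.5, 3. Wider alternatives were a single binary factor (prevalence 7–30%, risk ratio 2–10) and a composite risk score with SD 0.5 to 1.5 on the log-odds scale.

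**1. The plan's own sample size.** The two-sided pooled formula without covariates, per arm, is
(1.96·√(2p̄(1−p̄)) + 0.8416·√(p₀(1−p₀) + p₁(1−p₁)))² / (p₀−p₁)², with p̄ = 0.0216.
This gives 1175 per arm, 2350 in total, against 2274 stated. With RR 0.435, which rounds to 0.44, it gives 2300; the arcsine formula at 0.44 gives 2260. Power at 1137 per arm is 78.7%. The trial was therefore sized as a comparison of two proportions with no covariates, and a crude primary RR agrees with that.

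**2. Expected events and precision.** Per arm 2251/2 = 1125.5. Control events: 1125.5 × 0.03 = 33.8. Intervention events: 1125.5 × 0.0132 = 14.9. Total about 49.
SE(log RR) = √(1/33.8 − 1/1125.5 + 1/14.9 − 1/1125.5) ≈ 0.31.
The 95% interval extends by a factor of exp(1.96 × 0.31) ≈ 1.8 each way.

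**3. Size of chance imbalance.** For a covariate with 15% prevalence, the 95% range of the difference between arms is ±1.96·√(0.15 × 0.85 × 4/2251) = ±0.030, or 3 percentage points.

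**4. What adjustment changes (simulation).**

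| Assumed predictors | Reduction in variance of log RR | Gain in power |
|---|---|---|
| Four binary covariates | 1–3% at RR 0.44; up to 5% under the null | about 1–1.5 points |
| One binary factor, risk ratio 2–10 | 0–4% | −0.1 to +1.7 points |
| Composite score, SD 1.5 (very strong) | 7–10% | up to about 3 points |

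A hand check agrees in size. The expected z is 0.821/0.308 = 2.66, so power is Φ(2.66 − 1.96) ≈ 75.9%. Dividing z by √0.99 gives 76.3%, and by √0.97 gives 77.1%: gains of about 0.4 and 1.3 points.

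With four covariates, type I error was 4–5% for both analyses; over all scenarios it was about 3–6%. The crude RR showed no bias attributable to lack of adjustment. Covariates unrelated to PID caused no material loss.

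**5. How far the two estimates can differ in one trial.** With four covariates, the 95th percentile of the absolute difference in log RR was about 0.07 to 0.12, a factor of about 1.08 to 1.13. Against an SE of 0.31 that is 0.24 to 0.39 of a standard error.

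**6. Odds ratio against RR.** OR = (0.0132/0.9868)/(0.03/0.97) = 0.433, against RR 0.44, a 1.7% difference. An odds ratio conditional on a strong composite risk score came out at about 0.40–0.42.

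**The case against.** The strongest reply is that nothing here is wrong. Under simple randomisation the crude RR has no bias from imbalance, and its confidence interval already allows for chance differences between arms. It matches the way the trial was sized and leaves the fewest analytic choices open. All of this stands.

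The article condenses a fuller protocol, and a list of covariates is commonly left to that document or to an SAP, neither of which is shown. This also stands: the absence of a list is not itself a finding, and the point is offered only as an improvement. What the article does fix is a primary RR without covariates, with adjustment placed in a secondary analysis for BV alone.

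The gain rests on assumed associations. The article calls items such as age and partner number risk factors for chlamydia, not predictors of PID, and quantifies neither. This stands too, which is why ranges are given.

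A reader might infer that baseline pelvic pain or dyspareunia contaminates the outcome because the same symptoms flag possible cases. The documents do not support that as a bias. A flag only starts a record review, confirmation is made by physicians blind to arm, and baseline symptoms are balanced in expectation.

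On the logistic model, a fit can be standardised to give an RR, and the analysis is labelled exploratory. Both are true, but the plan does not say that standardisation is intended.

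**Conclusion.** The point holds as a minor improvement. The primary RR, read as crude, is a valid analysis; pre-specified adjustment would use baseline data already collected. Under the four-covariate assumptions the benefit is a 1–5% lower variance and about 1–1.5 points of power. It could be close to nothing if the items predict PID weakly, and somewhat larger if they predict it very strongly.

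A reader might infer that an unadjusted RR leaves a removable error in the answer, or that the primary result could be misleading. The documents do not support this. The typical extreme shift (a factor of 1.08 to 1.13) lies well inside an interval extending by a factor of about 1.8 each way. It could matter only for a borderline result.

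The mismatch in "exploratory logistic regression to adjust the RR of development of PID for the presence of baseline BV" is real on the page, because the raw coefficient is an odds ratio. A reader might take this as a material misstatement of the effect; at 3% risk the marginal odds ratio is within 2% of the RR, so it is not.

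**What to change.** **Primary analysis.** State whether the primary RR is crude or adjusted. The suggested form is a log-link (modified Poisson) model with robust standard errors, containing arm, age, number of partners in the past year, STI history, and baseline pelvic pain or dyspareunia. Fix the list before allocation is linked to outcome, and report the crude RR beside it. If the sponsor prefers the crude RR as primary, the same model can serve as a pre-specified supporting analysis.

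**BV analysis.** Use the same RR-scale model with BV added, or standardise the logistic fit to an RR, or keep logistic regression and call the result an odds ratio.

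**Cost.** A few sentences and one model; no new data. About 49 events limit the model to four or five covariates, and a simple rule is needed for missing baseline items. The BV correction stands whichever primary estimate is chosen.

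### The only planned BV analysis uses BV as a covariate for the screening effect, although the first secondary aim is BV's own association with PID

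*Protocol article*

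**What the plan says.** The protocol article lists, first under Secondary aims and again first under Secondary outcome measures, "The role of BV at baseline on the development of PID over 12 months". BV is the exposure and PID the outcome. The Background gives the reason: BV is of interest as a possible co-factor in PID that is associated with chlamydia.

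The Analysis Plan opens with the main comparison: "we will estimate the relative risk of developing PID in the 12 months after recruitment in the intervention group compared with the control". The next sentence is the only one on BV: "we will conduct an exploratory logistic regression to adjust the RR of development of PID for the presence of baseline BV". The plan then gives the second and third secondary aims one estimate each, with a 95% CI.

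Baseline chlamydia status is obtained in both arms. Intervention swabs are tested after randomisation and infected women are referred for treatment. For the other arm, the Intervention section says "Vaginal swabs from control women were stored at -80°C and analysed one year later". The baseline questionnaire (Recruitment) also records "age, ethnicity, age at first sexual intercourse, number of sexual partners in the past year, contraceptive use".

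**The concern.** The aim and the analysis point at different quantities. The aim asks how PID risk differs by baseline BV status. The analysis asks how the screening effect changes once BV is in the model. Only the first tells a reader anything about BV.

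The model does produce a BV coefficient, and an analyst would probably report it. The plan does not name it as the estimate, however, and the model as worded adjusts it for trial arm alone. If women with BV also carry chlamydia more often, some of the PID caused by chlamydia would be credited to BV. The document's own co-factor rationale makes chlamydia the first variable to consider. At stake is the interpretation of one exploratory aim, on which the Conclusion nonetheless promises new information.

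**Working it through.** The documents give no BV figure, so there is none to reproduce. The check sets the texts side by side and then sizes the consequences on stated assumptions.

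**1. Aims against estimates**

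| Secondary aim | Estimate in the Analysis Plan |
|---|---|
| 1. Baseline BV and PID | Screening RR adjusted for BV; no BV estimate or CI named |
| 2. Persistence or PID in untreated chlamydia | Proportion with 95% CI |
| 3. Incidence of chlamydia | Annual incidence with 95% CI |

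**2. What adjusting the screening effect for BV reveals**

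Inputs from Sample size calculations: "If we assume a 3% incidence of PID in the control group", RR 0.44 (a percent sign follows it in print) and 2274 women, taken as 1137 per arm. Assumed: BV prevalence 10–30%, true BV RR 1 to 3, and BV equally common in both arms.

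- Expected events: 1137 × 0.03 = 34.1 and 1137 × 0.0132 = 15.0, together about 49.
- Unadjusted screening OR: (0.0132/0.9868) / (0.03/0.97) = 0.433.
- A logistic regression of PID on arm and BV, fitted to expected counts, gives a BV-adjusted screening OR of 0.430 to 0.433 over the whole grid.

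The adjusted screening effect is thus almost the same whether BV triples PID risk or does nothing. The BV coefficient does differ: at 20% BV prevalence and a true RR of 2, its OR is 2.04 (95% CI 1.12–3.74). The information on BV lies in a coefficient that the plan does not name.

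**3. How far that coefficient could mislead if chlamydia is left out**

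All inputs are assumed: chlamydia in 12% of BV-positive and 5% of BV-negative women, PID risk 2% without chlamydia, PID risk r with untreated chlamydia, and no true BV effect.

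Control arm: apparent BV RR = (0.88 × 0.02 + 0.12 × r) / (0.95 × 0.02 + 0.05 × r).

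Both arms, equal in size, with treated women assumed to return to 2% risk: add 0.02 to the numerator and to the denominator.

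| r | Controls only | Both arms pooled |
|---|---|---|
| 9% | 0.0284/0.0235 = 1.21 | 0.0484/0.0435 = 1.11 |
| 16% | 0.0368/0.0270 = 1.36 | 0.0568/0.0470 = 1.21 |
| 23% | 0.0452/0.0305 = 1.48 | 0.0652/0.0505 = 1.29 |

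The pooled column is closer to the plan, which does not restrict the BV model to controls.

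Plausibility of the middle row, if BV prevalence is 20% (assumed): overall chlamydia is 0.2 × 12% + 0.8 × 5% = 6.4%, and control PID is 0.2 × 3.68% + 0.8 × 2.70% = 2.9%. Sample size calculations uses 7% (the earlier trial's chlamydia rate) and 3%.

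A second set of assumptions (chlamydia 5–7%; BV in 20% of women without and 40–50% of women with chlamydia; chlamydia-PID RR 5–10) gives 1.20 to 1.73 in the control arm.

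**4. Steps 2 and 3 must not be combined**

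Step 2 takes the planning effect, so the intervention risk is 1.32%. Step 3 sets a floor of 2% without chlamydia, so even complete removal of chlamydial PID gives a screening RR no lower than 2/3 = 0.67 at 3% control incidence. Each step illustrates one mechanism under its own inputs.

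**The case against.** The strongest reply is that the BV sentence is simply the analysis for the first aim, loosely worded. It comes first among the secondary analyses, in the same order as the aims, and any logistic model containing BV gives a BV odds ratio. This stands in part. A reader might infer that the trial would report nothing on BV, and the documents do not support that. What remains is that the stated target is the screening RR, and that aims 2 and 3 have named estimates while aim 1 has none.

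A second reply is that a condensed article need not list covariates; a full protocol or analysis plan, not shown here, may do so. This also stands. A reader might infer that confounders have been ruled out, but nothing in the Analysis Plan excludes them. The absence of a covariate list is therefore not the finding. Chlamydia is raised because the estimate needs restating anyway and the Background ties BV to chlamydial PID.

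Third, the bias figures rest on assumed inputs, and the pooled values (1.11–1.29) are small beside an illustrative interval of 1.12–3.74. This is correct, and the figures show direction and rough order only.

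Two further criticisms are tempting but should not be pressed. Logistic regression yields an odds ratio rather than the RR named, but at about 3% incidence the gap is negligible (0.433 against 0.44). Speaking of the presence of BV might seem to discard the three Nugent categories, but the article defines a positive category to which the phrase can refer, and the coding of the intermediate group is detail for an analysis plan.

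**Conclusion.** The concern holds as a mismatch between a stated aim and its stated analysis. The Analysis Plan makes BV a covariate for the screening effect, whereas the aim makes BV the exposure. The conclusion that the adjusted screening effect carries almost no information on BV rests on randomisation balancing BV and on the planning figures of 3% and RR 0.44.

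The BV coefficient from the model as written would be open to confounding by baseline chlamydia. On assumed inputs, with no true BV effect, the spurious RR is about 1.2–1.5 in controls and about 1.1–1.3 with both arms pooled. The documents give neither the link between BV and chlamydia nor the PID risks by chlamydia status, so the real size is unknown.

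The analysis is exploratory and the primary comparison is untouched. The change is worth making because it is cheap, not because the trial's main result depends on it.

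**What to change.** Replace the BV sentence in the Analysis Plan with wording such as: *In an exploratory logistic regression we will estimate the association between baseline BV and PID over 12 months, reported as an odds ratio with 95% CI, adjusted for trial arm, baseline chlamydial infection and the product of the two.*

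The product term is there because the trial arranges early treatment of chlamydia in one arm only, so baseline infection should carry a different PID risk in each arm. Add age or number of partners only as far as the event count allows; the planning figures imply about 49 events.

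Whether BV modifies the effect of chlamydia is a separate interaction question, and so few events would support it poorly.

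Cost: one sentence and one regression on data already collected. The downside is a few more model terms and a slightly wider interval for an exploratory estimate with few events. The primary analysis, already unadjusted as stated, needs no change.
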